### 2.6. Sample Size

The sample size is estimated based on changing the primary outcome (MoCA) according to the MCID/MCIC (Minimal Clinically Important Difference or Change), which has been established in a study performed by Wong et al. [60]. This Study suggested that a change of 2.0 can be considered as a reasonable minimum, clinically important difference for the main outcome variable (MoCA). Therefore, based on the previous study [32] examining mindfulness’s effect on the cognitive function of seniors with MCI, we estimated the effect size to be 0.5. Hence, we required 18 participants for each arm to have a power of 80% to detect statistical significance at a 5% level which was determined based on an analysis performed in the data of Wong et al. [32] using the Stata 17. Considering potentially a drop-out rate of 20%, 22 participants will be required to be allocated to each group. Therefore, the targeted total sample size will be 44 in order to sustain enough power in the present study.

## 3. Intervention Program

The Yoga based mindfulness intervention (YBM) will be based on video recording according to the following characteristics: (a) information about yoga and mindfulness will be delivered to seniors through specific exercises in each session (b) The mindful chair-based Hatha yoga will be used with an emphasis on proper Hatha yoga physical exercise or body awareness exercises [60,61] and mindfulness. If they find themselves unable to do a particular posture, they should be free to skip it and engage with their bodies with the attitude of kindness and acceptance, and after the completion of each posture, the participants will be asked to be mindful of muscles they will be tensing, stretching and which one will be used to keep their body balanced; (c) The mindfulness component will be based on (MBSR) guideline developed by Kabat-Zinn [48] which has been adapted from mindfulness protocol developed by Wong [32] for older people with MCI. The program will include both formal and informal practices. Participants will be taught to practice formal mindfulness techniques such as “body scan”, and “breath” meditations to observe and maintain attention on an object of meditation without judgment and reactivity even when one becomes distracted by drifting thoughts or unpleasant emotions and ‘loving-kindness’ meditation to cultivate kindness towards all beings, including oneself [32]. The informal practice involves spreading awareness to daily experiences such as mindful walking and eating [32]. The informal practice will also include mental exercises such as reading and solving puzzles, as well as being aware of daily interactions and other ADLs.

### 3.1. Procedures

Participants who would be assigned to the experimental group will receive the Yoga-based mindfulness intervention (YBM) for an hour, once weekly, for a total of 8 weeks. The YBM intervention program has been adapted to the needs, goals, and levels of understanding of MCI patients and will be executed based on a video that has been recorded by facilitators who have knowledge about yoga ([name]) and mindfulness ([name]) and who are different from those who will act as outcomes assessor and will be sent to the program attendees through WhatsApp application in order to watch and listen to on personal phones, computers or tablets. The control group will receive a passive psychoeducation with general information about wellness, self-care in health, and the promotion of exercise that will be delivered via text through the WhatsApp application each week.

### 3.2. Criteria for Stopping or Modifying Allocated Interventions

The neurologist who is in contact with patients for their treatment will be informed If patients allocated to the intervention or to the comparator present worsening of their physical or cognitive function at some point in the trial. Interventions will likewise be interrupted if a patient requests to withdraw from the study. Accordingly, this information will be informed to the affected participant and the Scientific Ethics Committee of the Clinical Hospital of the Universidad de Chile.

### 3.3. Plans to Improve Adherence to Intervention Protocols

Adherence to trial protocols will be ensured through participants’ satisfaction with the program. Therefore, they will be given telephone calls in order to keep a record of each session with the patients, and in case they have a doubt regarding the intervention program and contents. Moreover, the intervention program will be explained to their caregivers, and they will also be contacted in order to have their feedback about the intervention program.

### 3.4. Relevant Therapies and Interventions Allowedor Prohibited during the Trial

The patients would continue with their usual treatment, and that other interventions indicated by the doctor would also be allowed. They would be prohibited from receiving double treatment with yoga or mindfulness.

### 3.5. Participant Timeline

The participants’ timeline is displayed in Table 1.

## 4. Outcomes

Blind evaluators to randomization will assess all participants using the telephone-based survey before random assignment (Pre-test), the week following the last session of the intervention (post-test), and then after 3- and 6-months follow-up. It is noteworthy to mention that only the Montreal Cognitive Assessment outcome would be measured via live video call at baseline and post-intervention, 3- and 6-months follow-up.

### 4.1. Primary Outcomes

(1) Cognitive Function will be measured using a Spanish version of the Montreal Cognitive Assessment (MoCAS1-2) [62] is a short, easy-to-use, and useful test for diagnosing MCI and mild dementia. The test is valid in Chile, each of which has its own evaluation standard. The cut-off points for MCI and mild dementia are <21 and <20, respectively, with sensitivity and specificity rates of 75% and 82% for MCI and 90% and 86% for mild dementia.

### 4.2. Secondary Outcomes

(2) Physical function will be assessed using a:

(I) The Barthel Index (BI) [63] to measure performance in activities of daily living (ADL) [64]. Ten variables describe the capability of the person to carry out ten basic ADLs and mobility, a higher number reflecting a greater ability to function independently with mobility and self-care ADL.

(II) The Lawton Instrumental Activities of Daily Living Scale (IADL) [65] will be used to assess the independent living skills of participants. It measures functional ability as well as deteriorations and improvements over time. The protocols track eight functional domains through self-report, which measures everyday functional capability in the elderly. This would be performed by evaluating a more complex set of behaviors such as telephoning, shopping, food preparation, housekeeping, laundering, use of transportation, use of medicine, and financial behavior. Each area measured by the scale relies on either cognitive or physical function. Nonetheless, all require some degree of both [66].

(3) Psychological well-being will be assessed through the Pemberton happiness index (PHI) [67], which is a self-report questionnaire including two components of well-being. The first, with 11 items, assess the overall well-being and its four domains: general, psychological (eudaimonia), and subjective well-being (hedonia), as well as social welfare. The second, with 10 items, assess well-being experienced as a result of positive and negative experiences from the previous day. It is validated for the Spanish and Mexican populations. The internal consistency was 0.89 and the inter-item correlations varied between 0.31 and 0.56. The instrument has also been validated using samples from Chile, Cuba, and Uruguay, showing adequate psychometric properties [68].

(4) Geriatric Anxiety Inventory (GAI) [69] is a self-report measure designed for measuring general anxiety in older people. It consists of 20 items, measuring somatic, cognitive, and affective anxiety symptoms graded on a four-point scale of anxiety severity. Participants would be asked to rate anxiety symptoms by showing how often they have experienced each of the symptoms over the past week through a 4-point Likert scale ranging from 0 (not at all) to 3 (all time). Possible scores are in the range of 0 to 75, where high scores indicate high levels of anxiety [70]. It has been validated in Chile, showing a unidimensional factor structure with a high-reliability index of internal consistency with a = 0.931.

(5) The Geriatric Depression Scale (GDS-5) [71] is a depression screening measure that has been validated in a Chilean elderly population. It consists of 5-items questions for detecting geriatric depression. The five items are: (1) “Are you basically satisfied with your life?”, (2) “Do you often get bored?”, (3) “Do you often feel helpless?”, (4) “Do you prefer to stay at home rather than going out and doing new things?” and (5) “Do you feel pretty worthless the way you are now?”. A score of 2 or higher is indicative of possible depression. The GDS-5 demonstrated internal consistency of 0.73, construct reliability of 0.83, and one-dimensional structure [72].

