Dementia is usually preceded by a phase called mild cognitive impairment (MCI), a stage between the normal cognitive changes caused by aging and early dementia [10]. It encompasses a wide range of cognitive impairments such as memory, executive function, attention, language, or visuospatial skills [11]. Ample evidence has emerged that MCI has become equally prevalent among this segment of the population. A 2016–2017 National Health Survey reported that 10% of adults over 60 years old had suspected MCI, reaching 21% in those over 80 [12]. In the global sample, the prevalence of MCI for ages 60 to 64 years old was 6.7% [13]. However, in adults over 65 years, the prevalence increases to 14.8% and reaches 25.2% in those over 80 [13]. A number of studies have provided evidence that people with MCI are at greater risk of developing Alzheimer’s disease (AD) [14]; 5–15% of people with MCI are diagnosed with AD each year [15].

In addition, the elderly often experience depression and anxiety, which are common in people with MCI [16]. Recent findings indicate that people with MCI have a greater risk of developing the depressive disorder and anxiety disorder [17]. Previous studies show that the proportion of people with MCI who have depressive symptoms ranges between 36% to 63% [18]. Anxiety symptoms are equally frequent, with rates between 10 and 74% [16]. Chileans over 65 diagnosed for the first time with depression presented a greater link with cognitive impairment [19]. Other studies have also shown that depression and anxiety are risk factors for MCI [10,20] and that these conditions often precede the development of AD [21].

The decline in cognitive ability causes difficulty for older people in executing their daily activities [22] and has been associated with declines in functional status, quality of life, and increased dependency as well as mortality [23]. Albala [24] points out that the loss of physiological functioning because of aging reduces the resistance to stressors, leading to the greater vulnerability of older adults and to the development of frailty syndrome [24]. Frailty is strongly associated with cognitive impairment and depression in older Chilean adults [24].

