Specific Objectives:(1)To compare the change in cognitive function scores between older adults with MCI receiving a YBM intervention versus those receiving a PES intervention.(2)To compare the change in physical function scores between older adults with MCI receiving a YBM intervention versus those receiving a PES intervention.(3)To compare the change in well-being scores between older adults with MCI receiving a YBM intervention versus those receiving a PES intervention.(4)To compare the change in anxiety and depression scores between older adults with MCI receiving a YBM intervention versus those receiving a PES intervention.(5)To assess the correlation between cognitive function and physical function in older adults with MCI, controlling for psychological variables (depression, anxiety, well-being), and group (YBM intervention or participating in PES)

**Hypothesis 1.** *Older adults with MCI in the YBM intervention will have a different change in their cognitive function—as measured through MoCA assessment, before and after the intervention—than those in the PES intervention (with the same measures, before and after)*.

**Hypothesis 1.1.** *Older adults with MCI in the YBM intervention will have a different change in their physical function—as measured through the Barthel Index (BI) and The Lawton Instrumental Activities of Daily Living Scale (IADL) before and after the intervention—than those in the PES intervention (with same measures, before and after)*.

**Hypothesis 1.2.** *Older adults with MCI in the YBM intervention will have a different change in their well-being—as measured through the Pemberton happiness index, before and after the intervention—than those in the PES intervention (with the same measures, before and after)*.

**Hypothesis 1.3.** *Older adults with MCI in the YBM intervention will have will have lower anxiety and depression levels—as measured through the Geriatric Anxiety Inventory (GAI) and the Geriatric Depression Scale (GDS-5), before and after the intervention—than those in the PES intervention (with same measures, before and after)*.

**Hypothesis 2.** *Cognitive function will have an effect on physical function in older people with MCI, mediated by psychological factors (depression, anxiety, and well-being)*.

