## 6. Analysis

Descriptive analyses of relevant variables will be conducted for the total sample and for each group separately in order to assess the balance between the intervention group and the control group after randomization, thus, for categorical variables, the percentage and frequency will be presented for each intervention group, and for continuous variables, means and standard deviations for each intervention group, along with the mean difference between the groups, 95% CI, and *p* value will be presented. In order to determine if there are significant differences in pre and post-evaluation between groups, a mixed design analysis of the variance model with repeated measures (ANOVA) will be performed. One factor, between-subject factor, would consider a “group” (composed of older MCI in the YBM intervention group and older MCI in the active control group with PSE), and the other factor, repeated measures or within subjects’ factor, would be considered as “time” (composed by “pre”, “post”, & “follow up” measures) for primary and secondary outcomes.

In order to report the strength of the YBM intervention, the effect size will be calculated as well, level of significance will be set at *p* < 0.05 with 95% CI, Therefore, based on the repeated measure Anova, effect size calculation would be performed using the standardized mean difference (SMD), Cohen’s d [77]. According to the main outcomes of the study and the condition of the intervention program, since educational level, age and sex are considered as potential confounders o covariates, so they will be controlled at baseline in the Ancova model, and it will enter to model as factor or covariance using the continuous measure. Hence, effect size calculation would be performed using Partial Eta^2^. Moreover, subgroup analyses will be performed to test the possible mediator as well. All the analyses will be based on the intention-to-treat principle, accounting for loss-to-follow-ups, and will be performed using Stata, version 17.0.

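### The GDS-5 is at risk of a floor effect in a sample without psychiatric diagnoses, and the planned analysis does not adjust for the baseline score

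*Protocol article*

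**What the plan says.** Hypothesis 1.3 (protocol article, section 1) predicts that older adults in the intervention arm "will have lower anxiety and depression levels" than those receiving psychoeducation. Section 2.3 excludes anyone with a psychiatric clinical diagnosis but sets no upper limit on symptom scores.

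Section 4.2 measures depression with the GDS-5 alone: "It consists of 5-items questions for detecting geriatric depression". On its cut-off it says: "A score of 2 or higher is indicative of possible depression". On its reliability: "The GDS-5 demonstrated internal consistency of 0.73". Anxiety is measured separately by the GAI: "It consists of 20 items, measuring somatic, cognitive, and affective anxiety symptoms graded on a four-point scale of anxiety severity".

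Section 6 states that for primary and secondary outcomes "a mixed design analysis of the variance model with repeated measures (ANOVA) will be performed", with group as the between-subject factor and time as the within-subject factor. It adds an Ancova that names education, age and sex. It does not name the participant's own baseline score on the outcome.

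Section 1 gives the only figure on how common depressive symptoms are in this condition: "the proportion of people with MCI who have depressive symptoms ranges between 36% to 63" per cent. No baseline GDS-5 distribution is given, and only the MoCA is sized (section 2.6).

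**The concern.** The hypothesis is one of reduction. The entry rule removes people with diagnosed depressive disorder, who have most room to fall, and the scale has few steps. A participant who starts at 0 cannot improve, and one who starts at 1 can fall by one point only.

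A group-by-time contrast on such a score can miss a real benefit. A null GDS-5 result could then mean no effect or little room to show one, and the plan does not say how it would tell these apart. Depression is also one of the mediators in Hypothesis 2, so a compressed score would weaken that analysis too.

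**Working it through.** The plan has no GDS-5 calculation to reproduce. The check asks how many participants would start at the floor, and what the planned sample could detect.

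**Inputs from the article.** Five items, cut-off 2, internal consistency 0.73 (section 4.2); depressive symptoms in 36% to 63% (section 1); 18 evaluable per arm and 44 in total (section 2.6).

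**Assumptions.** Scores run from 0 to 5 (five yes/no items). Having depressive symptoms means scoring 2 or more. Scores follow a beta-binomial distribution.

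**Step 1, share at 0 or 1 with no effect of the exclusion.** This follows from the mapping alone: 1 − 0.36 = 64% and 1 − 0.63 = 37%, or about 16 to 28 of 44.

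**Step 2, share at exactly 0.** This needs the model.
- Inter-item correlation: r = α/[k − (k − 1)α] = 0.73/(5 − 4 × 0.73) = 0.73/2.08 = 0.351.
- Beta-binomial with s = (1 − r)/r = 1.849 and the mean solved so that P(score ≥ 2) equals the symptom rate.

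| Share ≥ 2 | Mean | SD | P(0) | P(0 or 1) |
|---|---|---|---|---|
| 36% | 1.32 | 1.53 | 44% | 64% |
| 63% | 2.36 | 1.73 | 20% | 37% |

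Check of the first row: the item mean is 1.32/5 ≈ 0.263, so b = (1 − 0.263) × 1.849 ≈ 1.363. P(0) is the product of (b + i)/(s + i) for i = 0 to 4 = 0.737 × 0.829 × 0.874 × 0.900 × 0.917 = 0.44.

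**Step 3, if the exclusion removes a fraction e of symptomatic people.** The article gives no value for e. The share left at 2 or more is p(1 − e)/[(1 − p) + p(1 − e)].
- e = 0.5: 0.18/0.82 = 22% and 0.315/0.685 = 46%. So 54% to 78% score 0 or 1, and the model puts 34% to 61% at 0.
- e = 0.75: 0.09/0.73 = 12% and 0.1575/0.5275 = 30%. So 70% to 88% score 0 or 1.

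**Step 4, detectable difference.** With 18 per arm, 80% power and two-sided 5%, the normal approximation gives 2.80 × √(2/18) = 0.93 SD; the t-test gives 0.96 SD. For one pre-post contrast, group-by-time is a comparison of change scores, which multiplies this by √[2(1 − ρ)]. Adjusting the follow-up score for baseline multiplies it by √(1 − ρ²). Here ρ is the baseline to follow-up correlation, which the article does not give. The last column uses the two rows of step 2 (no effect of the exclusion).

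| ρ (assumed) | Analysis | Detectable, SD | As share of baseline mean (36% / 63% rows) |
|---|---|---|---|
| 0.5 | change | 0.96 | 112% / 70% |
| 0.5 | adjusted | 0.83 | 97% / 61% |
| 0.7 | change | 0.74 | 86% / 55% |
| 0.7 | adjusted | 0.69 | 80% / 50% |

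The variance ratio of adjusted to change analysis is (1 − ρ²)/[2(1 − ρ)] = (1 + ρ)/2, that is 0.75 and 0.85. These formulas assume the same SD at both visits. When treated scores are pushed towards 0 the follow-up SD shrinks and change scores do worse than shown.

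**Step 5, simulation under this kind of model.** With 18 per arm and no group effect, t-tests and baseline-adjusted linear models rejected 4.5% to 5.4% of the time, against a nominal 5%. With a benefit built in, baseline adjustment raised power over change scores from 25% to 41% (ρ = 0.5) and from 32% to 51% (ρ = 0.7) in a floor-heavy case. In a milder case it rose from 44% to 62% and from 54% to 71%. These levels depend on the benefit assumed, so the direction of the gain is the result to rely on.

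**The case against.** The exclusion concerns a diagnosis, not symptoms. The article reports symptoms as common in this population and does not say whether those rates come from groups with diagnosed cases removed. How far the exclusion lowers scores is therefore unknown. This stands, and is why the conclusion starts from the unthinned rates.

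A reader might infer that Hypothesis 1.3 is close to untestable. The documents do not support that. At the upper symptom rate 63% would score 2 or more, and people who start at 0 can still worsen and so inform the contrast. The hypothesis already predicts a lower level than in the control arm, so less worsening counts and it needs no rewording.

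A reader might also infer that ANOVA on a six-value score gives unreliable standard errors. Under this model it does not: type I error stays close to 5%.

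A third inference is that anxiety scores are at the floor too. The GAI has 20 items, each graded in four steps, anxiety symptoms are put at 10% to 74% in section 1, and no floor can be derived from the text.

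Finally, this is a secondary outcome with no power claim, and the low sensitivity owes as much to 18 per arm as to the floor. That is fair and limits the weight of the point. An analysis plan could settle the details, but section 6 already states the model and its covariates, and the baseline score is not among them.

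**Conclusion.** The point holds for depression, as a risk of a floor effect combined with an insensitive analysis. At the article's own symptom rates about 37% to 64% of participants would start at 0 or 1, and 20% to 44% at 0. The first range rests on equating depressive symptoms with a GDS-5 score of 2 or more; the second also needs the beta-binomial model. Both rise if the exclusion removes symptomatic people, by an unknown amount.

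The planned test remains valid. At an assumed correlation of 0.5 and the unthinned rates, however, it could reliably detect only a difference of 70% to 112% of the modelled baseline mean. Adjusting for the baseline score gives a more precise comparison from data already scheduled. It reduces the problem without removing it, because no analysis creates room to improve.

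**What to change.** In section 6:

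- Analyse the GDS-5 as a between-arm difference in follow-up score, adjusted for the participant's baseline GDS-5. Do the same for the GAI with its own baseline; there the reason is precision, not a demonstrated floor.
- Optionally add an ordinal model for the GDS-5 as a sensitivity analysis. It is not needed for validity and offers no reliable gain in power.
- Limit the depression conclusion to people without a diagnosed psychiatric disorder.
- State that a null GDS-5 result will not be read as absence of effect if most participants start at 0 or 1.

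The cost is a few sentences. Both scales are already scheduled at baseline and at each follow-up (Table 1), so no data, visits or participants are added. The price is a narrower claim on depression.
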